## 1 INTRODUCTION

Acute pancreatitis (AP) is a common gastrointestinal disease with multiple causes, including gallstones, alcohol, and hypertriglyceridemia (HTG). Basolateral secreted or leaked pancreatic lipase-mediated triglyceride (TG) lipolysis may play an important role in the initiation and exacerbation of hypertriglyceridemia-associated acute pancreatitis (HTG-AP). This lipolysis process leads to the accumulation of free fatty acids (FFAs), which can cause cytotoxic injury to the pancreas. Notably, increased serum TG levels have been linked to worse clinical outcomes, manifesting as persistent systemic inflammatory response syndrome (SIRS) and organ failure.

On that basis, there have been some treatment strategies introduced to reduce serum TG levels, including noninvasive measures such as fasting, insulin, and heparin, as well as invasive blood purification techniques. Despite these interventions, international guidelines for the early management of AP did not give any recommendations regarding specific TG-lowering therapy due to the lack of solid evidence. Nonetheless, in some clinical settings, insulin with or without heparin has emerged as a common therapeutic approach for the early management of HTG-AP. Heparin, including low-molecular-weight heparin (LMWH), stimulates the release of endothelial lipoprotein lipase (LPL) into circulation, while insulin activates LPL and reduces the activity of hormone-sensitive lipase, thereby increasing the clearance of chylomicrons from plasma.

Although heparin with insulin is commonly used for lowering-TG in the treatment of HTG-AP, the efficacy and safety of LMWH plus insulin in HTG-AP remains controversial. Our previous RCT showed that LMWH plus insulin not only rapidly decreased the TG levels within 48 hours, but also significantly decreased the incidence of respiratory failure in HTG-AP patients. Additionally, heparin might reduce pancreatic necrosis and improve organ function, by its anti-inflammation and antioxidative properties. However, the bleeding risk of low-molecular-weight heparin (LMWH) was significantly lower than that of unfractionated heparin, and it exerts

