### 5.2 Secondary endpoints

All the endpoints are assessed and collected within one month after randomization including 1) New-onset organ failure including respiratory failure, renal failure, and circulatory failure; 2) Mortality; 3) The time to achieve the TG goal of <5.65 mmol/L, which will be detected using a fully automated blood biochemistry analyzer; 4) New-onset SIRS; 5) Necrotizing pancreatitis; 6) Infected pancreatic necrosis; 7) Sepsis;

8) Pulmonary infection; 9) Vein thrombosis; 10 ) Pseudoaneurysm; 11) Sinistral portal hypertension; 12) Abdominal compartment syndrome; 13) Cerebral hemorrhage; 14) Demand for mechanical ventilation; 15) Renal replacement therapy; 16) Percutaneous drainage of ascites; 17) Drainage of pancreatic necrosis; 18) Debridement of pancreatic necrosis; 19) Vascular interventional therapy; 20) Duration of intensive care unit stay; 21) Length of hospital stay; 22) Hospital costs.

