### 5.3 Safety endpoints

Safety outcomes include the new-onset bleeding, the rebound of serum TG, and drug-related adverse events (AEs). The new-onset bleeding is defined as new-onset abdominal or gastrointestinal bleeding occurring within two weeks after randomization. The rebound of TG is indicated by an increase in TG levels after prolonged use of heparin, with TG levels measured five days after randomization surpassing the TG levels measured within three days after randomization.

|                     | STUDY PERIOD |            |                 |       |       |       |       |           |
|---------------------|--------------|------------|-----------------|-------|-------|-------|-------|-----------|
|                     | Enrolment    | Allocation | Post-allocation |       |       |       |       | Close-out |
| TIMEPOINT           | Admission    | Day 0      | Day 1           | Day 2 | Day 3 | Day 4 | Day 5 | Day 28    |
| ENROLMENT           |              |            |                 |       |       |       |       |           |
| Eligibility screen  | X            |            |                 |       |       |       |       |           |
| Informed consent    | X            |            |                 |       |       |       |       |           |
| Allocation          |              | X          |                 |       |       |       |       |           |
| INTERVENTION        |              |            |                 |       |       |       |       |           |
| Two groups          |              |            | X               | X     | X     | X     | X     |           |
| ASSESSMENTS         |              |            |                 |       |       |       |       |           |
| Baseline variables  | X            | X          |                 |       |       |       |       |           |
| Primary endpoint    |              |            |                 |       |       |       |       | X         |
| Secondary endpoints |              |            | X               | X     | X     | X     | X     | X         |
| Safety endpoints    |              |            | X               | X     | X     | X     | X     | X         |

**Figure 2** The schedule of enrolment, interventions, and assessments of the study.

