### **8.2 Statistical analysis**

Three populations will be defined:

- Intention to treat (ITT) population: the set of all randomized participants.
- Per-protocol (PP) population: the set of all randomized participants, excluding cases with protocol violation, or withdrawal on patients willing.
- Safety analysis population: the set of all randomized participants.

Baseline variables will be presented as median with 25th-75th percentile or frequencies with percentages. The primary endpoint will be analyzed using the Chi-Squared Test. The secondary endpoints and safety outcomes will be compared by the Chi-Squared Test, Fisher's exact test, or Wilcoxon rank-sum test, as appropriate.

Results will be presented as relative risk (RR) with 95% confidence intervals (CIs). All statistical analyses will be performed using SPSS software (v26.0; SPSS Inc., Chicago, IL, USA), with significance set at a two-sided  $\alpha$  level of 5%.

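### Section 8.2 tests all 22 secondary endpoints at the same unadjusted two-sided 5% as the primary, with no hierarchy, no condition on the primary and no exploratory label

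*Protocol*

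**What the plan says.** Protocol section 8.2 assigns one chi-squared test to the primary composite. For the rest it states: "The secondary endpoints and safety outcomes will be compared by the Chi-Squared Test, Fisher's exact test, or Wilcoxon rank-sum test, as appropriate". The significance level comes in the closing sentence of the section, which begins "All statistical analyses will be performed using SPSS software" and ends "with significance set at a two-sided" level of 5%. That is the only significance level in the analysis section, and its scope is every analysis.

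Section 5.2 numbers the secondary endpoints from 1 to 22, ending "21) Length of hospital stay; 22) Hospital costs". Item 1 is "New-onset organ failure including respiratory failure, renal failure, and circulatory failure" and item 2 is mortality. These are the two parts of the primary composite defined in section 5.1.

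Nothing in the protocol gives an order of testing, names a key secondary endpoint, makes secondary tests depend on the primary result, divides alpha, or describes the secondary results as exploratory or descriptive.

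**The concern.** The protocol has a single confirmatory question, and it is properly fixed: one composite, one test, a sample size built on it and no interim analysis. The significance rule does not stop there. As written it treats a p-value below 0.05 for, say, pulmonary infection or hospital costs in the same way as one for the primary.

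With 22 such tests, one or more nominally significant results would not be surprising even if LMWH had no effect on any of them. Because organ failure and mortality are on the list, the rule would also let a component be called significant after a composite that was not. The trial is open-label, and some secondaries depend partly on clinical decisions (length of stay, intensive care stay, drainage procedures). That is a further reason not to give isolated p-values confirmatory weight. What is at stake is how the secondary results may be read. The primary conclusion is not at stake.

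**Working it through.** **Inputs from the protocol.** Number of secondary endpoints k = 22 (section 5.2). Level per test 0.05 two-sided (section 8.2), i.e. |z| > 1.96. 270 patients per arm (section 8.1). The protocol states no family-wise error rate for the secondaries, so there is no figure of its own to reproduce.

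**Inputs assumed.** The correlation between the 22 test statistics is not given. A common value rho from 0 to 0.8 is used. The secondary event rates are not given either; see step 4.

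**1. Expected number of false positives.** If no secondary outcome truly differs and each test has its nominal size, this is 22 × 0.05 = 1.1, whatever the correlation.

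**2. Independent tests.** P(at least one p<0.05) = 1 − (1 − 0.05)^22 = 1 − 0.95^22 = 1 − 0.324 = 0.676.

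**3. Correlated tests.** For equicorrelated normal statistics, with x a standard normal shared factor of density φ(x) and c = 1.96:

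P = 1 − ∫ [Φ((c − √rho·x)/√(1 − rho)) − Φ((−c − √rho·x)/√(1 − rho))]^22 φ(x) dx

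| rho | P(at least one p<0.05 among 22) |
|---|---|
| 0 | 67.6% |
| 0.3 | 56.9% |
| 0.5 | 43.9% |
| 0.7 | 30.1% |
| 0.8 | 23.1% |

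**4. Allowance for sparse events.** Several listed outcomes are likely to be rare (pseudoaneurysm and cerebral haemorrhage, for example), and tests on sparse tables fall short of their nominal size. With 270 per arm, and Fisher's test replacing chi-squared when expected counts are below 5, the true size is about 0.1% at an event rate of 0.5%, 1.1% at 1%, 3.9% at 2% and 5.0% at 3%.

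A patient-level simulation used 18 binary and 4 continuous endpoints and two assumed sets of event rates, 0.3% to 30% and 0.2% to 15%. Patient-level latent correlation was 0 to 0.7, with 2,500 replicates per setting. P(at least one) was 43% to 55% with the first set and 38% to 46% with the second. The mean number of false positives was about 0.6 to 0.8 instead of 1.1. Sparse data therefore reduce the problem without removing it.

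**5. Primary test.** It is one contrast with no interim look (section 8.3). Nothing in steps 1 to 4 changes its 5%.

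**The case against.** The strongest reply is that multiplicity rules and exploratory labels usually belong in the SAP, which is not shown. The closing sentence of 8.2 can be read as no more than a note on software and a conventional level. The endpoints are already labelled secondary, the sample size rests on the primary alone, and 8.2 already plans relative risks with 95% confidence intervals. Much of this stands: it is why the point is a cheap improvement and not a threat to the trial. It does not dispose of the point, because the protocol is not silent. It prescribes tests for the secondaries and one significance level for all analyses, and a SAP that called them exploratory would have to depart from that text.

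A reader might be tempted to go further in four ways that the document does not support.

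- Counting more than 22 tests. Item 1 of section 5.2 names three organ systems, but these are the same three that section 5.1 uses to define organ failure. Separate tests are not stated.
- Adding the three safety outcomes of section 5.3 to the tally. Leaving safety comparisons unadjusted is normal, because the worry there is a missed harm.
- Expressing the family-wise chance as a multiple of 5%. The protocol never presents its 5% as a family-wise rate.
- Citing the introduction's remark that the earlier trial "but also significantly decreased the incidence of respiratory failure in HTG-AP patients" as a sign of how secondary results will be used. The protocol does not say whether that result was primary, secondary or adjusted.

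Nor does any section say that a secondary result may stand in for a failed primary. The rule permits that reading but does not announce it.

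**Conclusion.** The point holds for the 22 listed secondary endpoints. Followed as written, section 8.2 declares any of them significant at p<0.05 without regard to the primary result or to the number of tests. If none truly differs, the chance of at least one such result is about 23% to 68%, and 44% at a correlation of 0.5. The range rests on assumed correlations between tests of 0.8 down to 0 and on each test having its nominal size; sparse events would lower the figures somewhat. No single value in the range can be taken from the protocol.

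It would be wrong to infer that the trial's type I error for its main question is inflated. The primary inference is unaffected.

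**What to change.** In section 8.2, replace the blanket significance statement with text to this effect: the two-sided 5% significance level applies to the primary endpoint only; secondary endpoints, including organ failure and mortality as components of the composite, are exploratory and will be reported as estimates with 95% confidence intervals, without adjustment for multiplicity and without claims of statistical significance. Add that safety outcomes will be reported as estimates with 95% confidence intervals, with no multiplicity adjustment.

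Any SAP should carry the same wording. The cost is one or two sentences, with no new data, patients or analyses. The downside is that isolated secondary p-values can no longer be presented as significant findings.

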### **8.3 Premature termination of the study**

No interim analysis will be performed. In this trial, the IDMC will examine safety variables every six months. The TMC will discuss, and if the adverse effects are confirmed, they will be reported to the medical ethic committee of the FAHNU. The medical ethic committee of the FAHNU will decide whether to terminate the trial, and audit trial conduct every 12 months independent from investigators.

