## **9 SAFETY MONITORING AND MANAGEMENT**

### **9.1 Trial management committee**

This trial will be coordinated by the trial management committee (TMC), which is formed comprising the principal investigator and the sub-investigators from all the participating centres. The TMC will be responsible for the day-to-day running, coordinating, and management of the trial. An expert clinical panel including members from each of the participating sites is formed to provide governance and audition for the study. This panel also will assist with making major clinical decisions.

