### **9.2 Independent Data Monitoring Committee**

The independent Data Monitoring Committee (IDMC) will manage data, data security and monitoring. An Independent Data and Safety Monitoring Committee (IDSMC) who are responsible for overseeing the safety and quality of the data. The committee is independent and has no competing interests with the research. The IDSMC considered protocol adherence, trial withdrawal, and safety monitoring and made recommendations for continuation of the trial.

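### Section 8.3 places an investigator-run step with no stated criterion between the independent committee's six-monthly safety review and the ethics committee that can stop the trial

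*Protocol*

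**What the plan says.** Five parts of the protocol bear on how a safety finding travels.

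- **Section 8.3, the review.** "In this trial, the IDMC will examine safety variables every six months". The safety variables are not listed there, and the section does not say whether they are tabulated by arm.
- **Section 8.3, what follows.** "The TMC will discuss, and if the adverse effects are confirmed, they will be reported to the medical ethic committee of the FAHNU". Then: "The medical ethic committee of the FAHNU will decide whether to terminate the trial". The same sentence gives that committee a duty to "audit trial conduct every 12 months independent from investigators".
- **Section 9.1, the TMC.** It runs the trial day to day, and its membership is described as one "which is formed comprising the principal investigator and the sub-investigators from all the participating centres". No independent member is mentioned.
- **Section 9.2, the independent committee.** The opening sentence gives an IDMC responsibility for data, data security and monitoring. The next introduces an IDSMC that oversees safety and data quality. Then: "The committee is independent and has no competing interests with the research", and "The IDSMC considered protocol adherence, trial withdrawal, and safety monitoring and made recommendations for continuation of the trial". The recipient of those recommendations is not named.
- **Section 9.3, single cases.** Investigators report serious adverse events on a separate form that goes to both the IDMC and the lead site's ethics committee. The TMC is not part of that route.

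**The concern.** An independent safety committee exists so that a judgement on accumulating safety can be made, and passed on, by people who do not recruit or treat the participants. Section 8.3 describes one path from the periodic review to the body that can stop the trial, and that path goes through the people who do both. Under section 4.1 the site sub-investigators also carry out randomization, and under section 4.2 investigators know the treatment given.

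The word *confirmed* carries the weight, and the protocol does not define it. It does not say what would count as confirmation, who gives it, by when, or what happens if the independent committee and the TMC disagree. A finding that the TMC judged unconfirmed, or was still discussing, would have no described way forward.

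At stake is participant safety in a trial of an anticoagulant, where the introduction itself raises pancreatic haemorrhage as a worry with prolonged heparin use. The independence claimed in section 9.2 is also at stake, because section 8.3 gives that committee's recommendations no role.

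**Working it through.** No formula applies to a reporting line, so the check sets the sections side by side. The only arithmetic is for scale.

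**1. The path for the periodic review.** IDMC examines (8.3) → TMC discusses (8.3; composition in 9.1) → adverse effects reported if confirmed (8.3) → ethics committee decides on termination (8.3). No section describes a path for this review that omits the second and third steps.

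**2. Who confirms.** The clause is passive. The TMC is the only body named in the sentence before the recipient, so it is the natural reading, but the text does not say so outright, nor does it say that reporting happens *only* on confirmation.

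**3. Where the independent committee's recommendations go.** Section 9.2 says that the committee "made recommendations for continuation of the trial". Section 8.3 does not mention such a recommendation, and section 9.2 neither routes it through the TMC nor sends it to the ethics committee. The two sections do not strictly contradict each other, since one body may recommend and another decide. They do leave the link between them unstated.

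**4. One committee or two.** Sections 8.3 and 9.3 give the six-monthly safety examination to the IDMC. Section 9.2 gives the IDMC a data role and gives safety oversight and recommendations to the IDSMC. If these are one body, the name is inconsistent. If they are two, the protocol does not say whether the body that recommends sees what the other examines.

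**5. Do the other channels carry the review's findings?**
- *Serious adverse event forms (9.3).* They reach the ethics committee directly, one case at a time. At the design rates in section 8.1 with 270 per group, 270 × 0.083 ≈ 22 and 270 × 0.1786 ≈ 48 patients would have organ failure or die. Such events are therefore expected in both groups from the disease alone, and a pattern is hard to see from single forms. Section 5.3 also lists safety outcomes that need not be serious events, such as triglyceride rebound, and no direct route to the ethics committee is described for these.
- *Ethics committee audit (8.3).* It covers trial conduct. It is not described as a review of safety data or as receiving the IDMC's findings.

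**6. Scale.** With recruitment estimated at 36 months, 36 / 6 = 6 IDMC reviews and 36 / 12 = 3 ethics committee audits. The TMC step applies to the six reviews. These counts show how often it would operate; they do not measure harm.

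**The case against.** The strongest reply is that the decision to stop rests with the ethics committee and not with the investigators, that this committee receives serious adverse event forms without any TMC step, and that it audits the trial yearly and independently. Section 9.2 does not send the independent committee's recommendations through the TMC, and nothing forbids direct reporting. If the IDSMC is a separate body, its recommendations could be a second channel. On this view the matter is one of clarification, with no effect on sample size, alpha, endpoints or analysis.

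Much of this stands, and it rules out two readings that a reader might infer. The first is that independent oversight is undone, with investigators controlling everything the ethics committee learns. Sections 8.3 and 9.3 show otherwise: the possible filter acts on the periodic review, not on all safety information. The second is that investigators see accumulating safety results by arm while they recruit and assess outcomes. No section says that the review is split by arm or what material the TMC receives, so a claim of resulting bias would rest on an assumption.

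What does not stand is the suggestion that there is nothing to correct. Section 8.3 is not silent: it states a sequence, and following that sequence puts investigators ahead of the ethics committee. That direct reporting is not forbidden does not amount to providing for it, and the two safeguards are not described as carrying what the periodic review finds.

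**Conclusion.** The concern holds in a limited form. The one described route from the six-monthly review to the body that decides on termination includes discussion by a committee of unblinded investigators and an undefined confirmation. This allows delay or filtering of the independent committee's periodic findings and fits poorly with section 9.2. About six reviews during recruitment would be affected. Individual serious adverse event reporting and the yearly audit reduce the risk without closing the gap.

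The conclusion rests on two readings: that the TMC does the confirming, which is natural but not explicit, and that no other document sets out a direct line for the committee. If another body confirms, the protocol should name it. The point should be corrected, as it bears on participant safety and costs little. It does not alter the statistical design.

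**What to change.** Reword sections 8.3 and 9.2, and align the committee name in 9.3:

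- State whether IDMC and IDSMC are one body, and use one name throughout. If they are two, say which examines the safety variables and which recommends.
- State that after each six-monthly review the independent committee sends its written recommendation directly to the ethics committee, without prior TMC confirmation.
- State that the TMC is informed of that recommendation in parallel and may comment to the ethics committee, but that its discussion does not hold the report back.
- As a precaution, state that the TMC receives no by-arm data, since the protocol does not say what it receives.

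The cost is wording only, submitted for ethics re-approval as section 6.2 requires for any amendment. It needs no extra staff and changes neither sample size, treatment nor analysis.
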